### Sustainability

Throughout the implementation phase, the study team will periodically meet with health system representatives and clinic managers to develop practical solutions to manage any additional clinical burden. With the transition of the Early Arm health systems to sustainability, the study-specific TTS will no longer provide counseling. Rather, health systems will need to have their own TTS (whether established or newly hired) to deliver counseling to sustain the *Break Free* program. An important component of sustainability will be recovering maximum allowable costs for smoking cessation counseling from health insurers. Thus, providers will be trained on how to bill insurance companies for tobacco cessation counseling. In the sustainability phase, current billing and pharmacotherapy practices of each health system, potential barriers in optimizing reimbursement, and their potential solutions will be documented. The Biostatistics and Evaluation core will assist in data extraction for these measures.

Prior to the sustainability period, the other two interventions that are part of *Take CARE* (addressing HPV vaccination and cervical cancer screening) will be “bundled” with the *Break Free* smoking cessation intervention as part of a multifaceted cervical cancer prevention program. We will provide a refresher training for all clinic staff and providers that reviews how to implement all three interventions with patients. We will also train clinic staff and providers on how to bill for services provided specific to all three interventions.

### Program evaluation

*Take CARE* program evaluation will include documentation and monitoring of implementation (process evaluation), assessment of progress in reaching goals and objectives (outcome evaluation), and the extent to which interventions are adopted by clinics and sustained over time (sustainability evaluation). Consequently, the Survey and Data Collection and Biostatistics and Evaluation cores will support evaluation for each of the three *Take CARE* initiatives separately as well as the *Take CARE* program overall. Evaluation at the overarching program level, will investigate the relative contributions of individual, community, clinic, and intervention effects on uptake of the three *Take CARE* initiatives by participating clinics. For this study protocol, we present detailed information on the *Break Free* project evaluation, including measures, sample parameters, and statistical analyses.

### Process, outcome, and sustainability measures

#### Process evaluation

##### Provider outcomes

*A*cceptability of the *Break Free* intervention will be examined by estimating adoption by providers and staff. These provider-level outcomes will include self-reported changes in the delivery of AAR and the rate of referrals to the in-clinic TTS.

##### Patient outcomes

Fidelity to the intervention will be assessed two ways. First, 10% of women will be randomly selected and called by a study staff person the day after *Break Free* cessation phone counseling and asked standardized questions about the content of the call. Second, self-administered, anonymous patient post-visit surveys will be completed throughout the implementation phase. These fidelity surveys will ask patients to report whether the provider: (1) asked about tobacco use; and if a smoker, (2) advised the individual to quit; (3) discussed cessation; and (4) referred the smoker to counseling. The proportions of patients being asked, advised, and referred are the outcomes.

#### Outcome evaluation

##### Provider outcomes

The primary outcome among providers is adoption of the AAR components, measured by self-report on the provider survey administered at the end of the implementation phase. We will also assess responses to the knowledge items on the survey (pre vs. post-training, and follow-up).

##### Patient outcomes

The primary outcomes among *Break Free* patient participants include self-reported: (1) 7-day point prevalence abstinence; (2) 7-day floating abstinence during any period since last assessment; (3) prolonged abstinence (no smoking after a 2-week grace period after the quit date); and (4) at least one 24-h quit attempt. A 24-h quit attempt is an important endpoint given that it is associated with a greater likelihood of future cessation [39]. Secondary outcomes among *Break Free* participants include use of pharmacotherapy and number of counseling sessions completed.

#### Sustainability evaluation

*Sustainability* will be measured by: (1) documentation of patient tobacco use status in the EHR; (2) TTS self-report of continued smoking cessation counseling; and (3) billing-related documentation of number of counseling sessions billed for overall and for each smoker who has at least one *Break Free* counseling session. The Survey and Data Collection core will support EHR and billing data extraction. With the support of the Biostatistics and Evaluation core, we will also assess cost-effectiveness by considering costs of each component including pharmacotherapy, clinic counselor time and training, smoking cessation counselor time and training, telephone and material costs, and other administrative costs.

### Sample size and power analysis

The sample size for the primary outcome (i.e., smoking cessation among female smokers) is 51 female smokers per health system, for a total of 510 participants. This sample size is based on a two-sample test of the 7-day point prevalence abstinence at 6 months with power calculated using a standard cluster randomized design formula [44]. Assuming a 10% quit rate in the delayed group, a 25% quit rate in the early intervention group, and a conservative estimate of the intraclass correlation of 0.017, a total of 10 health systems, equally randomized to Early and Delayed Intervention groups, a total of 43 smokers per health system will provide 80% power at a two-sided significance level of 5%. The sample size was inflated to 51 smokers per health system (or 510 total) to account for an estimated 20% dropout.

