### Statistical analyses

#### Missing data

We recognize that despite efforts to minimize dropout and missing data, there will be subjects who miss assessments or drop out of the project prior to completion. To avoid biases due to relationships between dropout and patient characteristics, we will use multiple imputation methods appropriate for multilevel data [45] to impute missing outcomes. Imputation models will include health system, intervention group, and any patient factors that differ between those who dropped out and those completing the study. The number of imputed data sets will equal the dropout percentage as recommended by White and colleagues [46]. Results from the imputed data sets will be combined using Rubin’s rules [47].

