#### Patient outcomes

For all patient outcomes, we will conduct ITT analyses. We will assume that non-responders to surveys will be continued smokers.

Hierarchical (mixed) models will be used to compare smoking cessation outcomes at 6- and 12-months between female smokers in the Early and Delayed Arm health systems. Logistic models will be used for the binary outcomes, including the point prevalence, floating and prolonged abstinence, and at least one 24-h quit attempt. Subsequent analyses will adjust for patient-level characteristics in comparing smoking cessation at 6 and 12 months among patients in the Early and Delayed Arm health systems.

Mixed models will be used to assess measures of participant satisfaction with *Break Free*, using random effects for health system and primary provider. Subsequent analyses will add patient characteristics in order to evaluate whether satisfaction with the *Break Free* program differs by these characteristics.

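### 51 smokers per health system covers about 16% dropout, not the stated 20%; the effect on power is small, but the basis of the 10% and 25% quit rates should be stated

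*Protocol article*

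**What the plan says.** All the design figures are in the protocol article under Sample size and power analysis. The comparison is 7-day point prevalence abstinence at 6 months: "Assuming a 10% quit rate in the delayed group, a 25% quit rate in the early intervention group", with "a conservative estimate of the intraclass correlation of 0.017" and "a total of 10 health systems, equally randomized to Early and Delayed Intervention groups". On these inputs "a total of 43 smokers per health system will provide 80% power at a two-sided significance level of 5" percent. The dropout allowance follows: "The sample size was inflated to 51 smokers per health system (or 510 total) to account for an estimated 20% dropout". How the inflation was done is not stated, and the cluster formula is given only by citation.

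Two later passages govern participants without an outcome. Under Statistical analyses, Missing data: "we will use multiple imputation methods appropriate for multilevel data [45] to impute missing outcomes". Under Statistical analyses, Patient outcomes, after specifying intention-to-treat: "We will assume that non-responders to surveys will be continued smokers".

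**The concern.** A dropout allowance should leave the required number once the stated loss has occurred. Here 51 less 20% is below 43, so the enrolment target, the dropout rate and the evaluable number cannot all stand together. The total of 510 is repeated in the abstract, so readers will rely on it.

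A second matter affects how the power figure should be read. Inflating for dropout treats lost participants as leaving the analysis, yet both missing-data passages keep them in. If they are kept as smokers, what matters is whether the assumed 10% and 25% already include them as smokers, and the sample size section does not say. At stake are the accuracy of a published design figure and the clarity of the power statement. The trial's design itself is not in question.

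**Working it through.** **Inputs** (all from Sample size and power analysis): p₁ = 0.10, p₂ = 0.25, ICC = 0.017, 5 systems per arm, two-sided α = 0.05, m = 43 evaluable per system, 20% dropout, 51 enrolled per system.

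**Step 1: reproduce the 43.** The design effect is DE = 1 + (m − 1) × 0.017, and the effective number per arm is 5m/DE. At m = 43, DE = 1.714 and the effective number is 215/1.714 = 125.4.

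- *Noncentral t, 8 df, unpooled variance.* The variance sum is 0.09 + 0.1875 = 0.2775. The standard error is √(0.2775/125.4) = 0.0470, so the noncentrality is 0.15/0.0470 = 3.19. Against the critical value 2.306, power is 79.7%.
- *Formula that sets aside one cluster per arm* (4 instead of 5, normal test, pooled variance under the null). Power at 43 is 80.3%, and 43 is the smallest m that reaches 80%.
- *Plain normal approximation with the design effect.* Power at 43 is 88.3%, and 30 per system would be enough for 80%. This is not what gave 43.

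The 43 is therefore sound under a correction for few clusters.

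**Step 2: check the dropout allowance.**

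- Left after 20% loss from 51: 51 × 0.8 = 40.8 per system, or 408 in total against 430 needed.
- Needed to retain 43: 43/(1 − 0.20) = 53.75, so 54 per system and 540 in total.
- Shortfall: 3 per system, 30 overall (30/540 = 5.6%).
- Dropout that 51 does cover: 1 − 43/51 = 15.7%.

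**Step 3: power if dropouts leave the analysis.** At m = 40.8, DE = 1.6766 and the effective number is 204/1.6766 = 121.7.

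| Method | m = 43 | m = 40.8 |
|---|---|---|
| Noncentral t, 8 df | 79.7% | 78.5% |
| One cluster per arm set aside | 80.3% | 79.1% |
| Plain normal (does not reproduce 43) | 88.3% | 87.3% |

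The loss is about 1.2 points under either method that reproduces the plan. With only 10 clusters, a few participants more or fewer per cluster change power little.

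**Step 4: power if non-responders are kept as smokers.** All 51 per system are analysed, so DE = 1.85 and the effective number is 255/1.85 = 137.8. The protocol does not say which of these readings of 10% and 25% applies:

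- *They already count non-responders as smokers.* The comparison stays 10% against 25%. Power is about 83% (noncentral t) or 83.9% (one cluster per arm set aside).
- *They are rates among responders, with an assumed 20% non-response in each arm.* The analysed rates become 0.10 × 0.8 = 8% and 0.25 × 0.8 = 20%. The variance sum is 0.0736 + 0.16 = 0.2336, the standard error √(0.2336/137.8) = 0.0412 and the noncentrality 0.12/0.0412 = 2.91. Power is 72.4% (noncentral t). At 54 per system it would be 73.7%, so correcting the inflation does not address this scenario.

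**The case against.** The strongest reply is that the slip has almost no consequence. Power moves by about one point, and the method that reproduces 43 gives 79.7% there, so the quoted 80% is already rounded. The cited cluster formula cannot be seen, so the small-cluster methods are inferred from the fact that they return 43. The 40.8 also supposes a completers-only analysis, which the protocol does not plan. All of this stands, and it limits the point to a correction of a stated figure. It does not rescue the sentence, because no rounding turns 53.75 into 51. The 87% from the plain normal formula is little reassurance, since that formula would have required only 30 per system.

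A reader might go further and infer three things that the document does not support.

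- *That the trial fails to deliver its 80% power.* The drop to 78.5% or 79.1% is too small to carry that claim.
- *That power is really 72%.* This needs 10% and 25% to be responder rates and non-response to be 20% in both arms. The protocol calls them simply quit rates. Given its intention-to-treat rule, they can equally be read as already counting non-responders as smokers, which gives about 83%. The dilution is also a separate matter from the inflation slip.
- *That 43 was multiplied by 1.2.* That product is 51.6, which gives 51 only if truncated. The protocol does not describe the step, so this is a guess, and the error does not depend on it.

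**Conclusion.** The stated dropout allowance is wrong as written, and the error is minor. The 15.7%, 40.8 and 54 follow from the protocol's own 43, 51 and 20% and need no further assumption. The power figures rest on the stated rates and ICC, on equal cluster sizes and on the small-cluster methods that reproduce 43. Under these, 20% loss with a completers-only analysis costs about 1.2 points.

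A material loss of power is not shown. Under the rule that counts non-responders as smokers, power at 51 per system ranges from about 72% to about 83% (noncentral t), depending on a definition that the sample size section leaves open. That definition should be stated.

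**What to change.** In Sample size and power analysis, replace the dropout sentence with one of two accurate statements: that 51 per system (510 in total) allows for about 16% dropout from 43, or that at 20% dropout about 41 per system remain and power is about 78.5% to 79%.

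Add one sentence saying whether the 10% and 25% already count non-responders as smokers, and quote power on that basis: about 83% at 51 per system if they do, or about 72% if they are responder rates with 20% non-response in each arm. If multiple imputation is the primary handling of missing outcomes, say so and tie the power statement to it.

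The cost is one or two reworded sentences. The enrolment target, design and analysis stay unchanged. The stated dropout allowance, or the stated power, becomes slightly less favourable.

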### Statistical analyses

#### Missing data

We recognize that despite efforts to minimize dropout and missing data, there will be subjects who miss assessments or drop out of the project prior to completion. To avoid biases due to relationships between dropout and patient characteristics, we will use multiple imputation methods appropriate for multilevel data [45] to impute missing outcomes. Imputation models will include health system, intervention group, and any patient factors that differ between those who dropped out and those completing the study. The number of imputed data sets will equal the dropout percentage as recommended by White and colleagues [46]. Results from the imputed data sets will be combined using Rubin’s rules [47].

#### Provider outcomes

For all provider outcomes, we will conduct intent-to-treat analyses (ITT), such that all participants who are randomized will be included in statistical analyses.

Mixed logistic regression models, with random effects for provider and clinic, will be used to assess the proportion of patients receiving AAR over the time periods pre-intervention, during intervention and in the post-intervention periods.

Mixed models will be used to assess measures of staff and provider satisfaction with the program, using random effects for health system. Subsequent analyses will add provider characteristics in order to evaluate whether satisfaction with *Break Free* differs by these characteristics. Mixed models will be used to evaluate changes in provider knowledge and attitudes over time, using random effects for health system.

#### Patient outcomes

For all patient outcomes, we will conduct ITT analyses. We will assume that non-responders to surveys will be continued smokers.

Hierarchical (mixed) models will be used to compare smoking cessation outcomes at 6- and 12-months between female smokers in the Early and Delayed Arm health systems. Logistic models will be used for the binary outcomes, including the point prevalence, floating and prolonged abstinence, and at least one 24-h quit attempt. Subsequent analyses will adjust for patient-level characteristics in comparing smoking cessation at 6 and 12 months among patients in the Early and Delayed Arm health systems.

Mixed models will be used to assess measures of participant satisfaction with *Break Free*, using random effects for health system and primary provider. Subsequent analyses will add patient characteristics in order to evaluate whether satisfaction with the *Break Free* program differs by these characteristics.

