### Hybrid effectiveness-implementation study design

In this cluster randomized trial, health systems are stratified by state and then randomized in a 1:1 ratio to either an Early Arm or Delayed Arm. To reduce the risk for contamination, within each stratum, health systems are randomized into Early Intervention or Delayed Intervention arms. All clinics within each health system are randomized to the same condition (Early or Delayed Intervention). Neither health systems nor study participants are blinded to their intervention assignment.

Figure 2 outlines the timeline for study implementation and evaluation. Following a planning phase (months 1–23; not shown in the figure), *Break Free* will be implemented in Early Arm health systems over a 12-month period. After this 12-month period ends, research staff will train Early Arm health systems on how to bill for brief counseling (AAR) and smoking cessation phone counseling, as well as how to implement *Break Free* using their own staff and resources as they transition to a full sustainability period. During this period, Early Arm health systems will also learn how to “bundle” all three *Take CARE* projects addressing smoking cessation, HPV vaccination, cervical cancer screening as part of an integrated cervical cancer prevention program disseminated by clinics. Delayed Arm health systems will initially enroll female smokers into an observational study, which will allow estimation of the smoking cessation rate in the target population receiving usual care. This group of women will serve as the comparison for the “effectiveness” of *Break Free*. After 12 months, while the Early Arm health systems are in the sustainability period, Delayed Arm health systems will implement *Break Free*, delivered by our research staff. After that 12-month period ends, they too will then shift to a sustainability period. Implementation of *Break Free* will be evaluated through randomly sampled patient assessments of provider fidelity to AAR and, for women enrolled in *Break Free* TTS counseling, assessments of TTS fidelity to *Break Free* counseling.

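### The cessation comparison rests on 10 randomized health systems, but the analysis text commits to no small-sample reference; large-sample inference would run at about 7–9% type I error instead of 5%

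*Protocol article*

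**What the plan says.** In the protocol article, under Hybrid effectiveness-implementation study design, "health systems are stratified by state and then randomized in a 1:1 ratio", and all clinics in a system share one arm. Under Sample size and power analysis there is "a total of 10 health systems, equally randomized to Early and Delayed Intervention groups", so the arm comparison has 5 + 5 independent units.

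The same section gives the assumed quit rates: "Assuming a 10% quit rate in the delayed group, a 25% quit rate in the early intervention group". For the clustering of smokers within systems it takes "a conservative estimate of the intraclass correlation of 0.017". It concludes that "a total of 43 smokers per health system will provide 80% power at a two-sided significance level of 5" (per cent), with "power calculated using a standard cluster randomized design formula". Whether that formula uses normal or t quantiles is not stated.

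Under Statistical analyses, Patient outcomes, "Hierarchical (mixed) models will be used to compare smoking cessation outcomes at 6- and 12-months", with logistic models for the binary outcomes. No test statistic, denominator degrees of freedom or small-sample method is given, and none is excluded. The random-effect level for this comparison is also not named, although the article names it for other models: provider and clinic for delivery of Ask, Advise and Refer, health system for provider satisfaction and knowledge, and health system and primary provider for patient satisfaction.

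**The concern.** Arm does not vary within a health system, so precision for the arm effect is limited by between-system variation, and that variation is estimated from only ten systems. Large-sample inference for a mixed logistic model treats the estimated between-system variance as if it were known. With five systems per arm the estimate is poor and is often exactly zero. The test then rejects too often and the confidence interval is too short.

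At stake is whether a result reported at the 5% level has that error rate. The sample size appears to have been chosen with few clusters in mind. If the analysis drops that allowance, the trial gives up error control that the design had already paid for.

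**Working it through.** **Inputs** (Sample size and power analysis): quit rates 0.10 and 0.25, ICC 0.017, 5 systems per arm, 43 analysed per system, two-sided 5%, 80% power.

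**1. Reproducing the stated power**

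- Design effect: 1 + (43 − 1) × 0.017 = 1.714.
- Effective sample per arm: 5 × 43 / 1.714 = 125.4.
- Unpooled variance sum: 0.10 × 0.90 + 0.25 × 0.75 = 0.2775.
- Standard error: √(0.2775 / 125.4) = 0.0470.
- Noncentrality: 0.15 / 0.0470 = 3.19.
- Normal reference: Φ(3.19 − 1.96) = 0.89.
- t reference on 2 × (5 − 1) = 8 df (critical value 2.306): power 0.797.

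**2. Which formulas give 43 per system**

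The pooled normal formula needs, per arm without clustering, (1.96 × √(2 × 0.175 × 0.825) + 0.8416 × √0.2775)² / 0.15² = 99.5. With k systems per arm, solve k·m / (1 + (m − 1) × 0.017) = 99.5, which gives m = 99.5 × 0.983 / (k − 99.5 × 0.017).

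- k = 5 (no allowance): 97.8 / 3.31 = 29.6, so 30.
- k = 4 (one of the five systems per arm set aside as the few-cluster allowance): 97.8 / 2.31 = 42.4, so 43.

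| Formula | Smallest m for 80% power |
|---|---|
| Normal, unpooled | 29 |
| Normal, pooled | 30 |
| Normal, continuity-corrected | 37 |
| Normal, unpooled, plus one cluster per arm | 41 |
| Normal, pooled, plus one cluster per arm | 43 |
| t on 8 df, unpooled | 44 (79.7% at 43) |

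Only the versions with a few-cluster allowance come close to 43.

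**3. Type I error of the planned model**

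System quit counts were simulated as beta-binomial, 5 versus 5, with equal quit rates. A random-intercept logistic model was fitted by maximum likelihood (25-point quadrature), with 3,200 trials per setting. The Monte Carlo standard error near 9% is √(0.09 × 0.91 / 3200) = 0.5 points.

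| Quit rate, ICC, m | Wald z | Likelihood ratio | Same model, t(8) | Cluster-level t-test |
|---|---|---|---|---|
| 0.10, 0.017, 43 | 8.8% | 7.5% | 4.5% | 4.8% |
| 0.10, 0.017, 51 | 9.5% | 7.9% | 5.2% | 5.0% |
| 0.175, 0.017, 43 | 8.6% | 7.4% | 4.6% | 5.0% |
| 0.10, 0.001, 43 | 4.1% | 3.9% | 1.7% | 5.2% |
| 0.10, 0.05, 43 | 10.5% | 8.1% | 5.6% | 3.7% |
| 0.10, 0.10, 43 | 15.8% | 9.5% | 10.1% | 4.2% |

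A further run of 4,000 trials at ICC 0.017 and 51 per system gave 9.1% (Wald z), 4.9% (t(8)) and 5.0% (cluster-level t-test). At ICC 0.005, Wald z runs at about 6%. As an analytic check, 2 × P(t₈ > 1.96) = 8.6%. At ICC 0.017 and 43 per system, the between-system variance was estimated as zero in about a third of trials.

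**4. Interval width.** For a given standard error, a normal-based interval is 1.960 / 2.306 = 0.85 times the length of the t(8) interval.

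**5. Power after the change.** At 10% versus 25% and 43 per system, simulated power is 85% for the model with t(8) and 80% for the cluster-level t-test. The analytic t(8) figure is 79.7%.

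**The case against.** The strongest reply is that the article does not prescribe a faulty test. It names a model class and leaves the reference distribution open. Such detail is commonly left to the statistical analysis plan, which is not shown, and the same planned model with t(8) holds its level at the protocol's ICC. This stands: the 7–9% is conditional on large-sample inference being used. A reader might infer that the protocol specifies a Wald z test, but it does not.

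A reader might also infer that 43 can only have come from a t calculation on 8 df, so that design and analysis are shown to use different tests. The figures do not support that. The pooled normal formula with one extra cluster per arm gives exactly 43, while t(8) falls just short of 80% there and needs 44. The cited formula is not visible. Both routes do contain a few-cluster allowance, and that is as far as the inference goes.

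The protocol calls its ICC conservative. If the true value is lower, the excess shrinks, and near zero it vanishes.

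Finally, a reader might take the article's silence on state in the analysis as proof that the strata are ignored. A condensed article does not establish that.

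What survives is that both usual large-sample tests of the stated model miss 5% at the protocol's own ICC, and that the text leaves them open although the sample size allows for few clusters.

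**Conclusion.** The point holds in conditional form, as a cheap and worthwhile clarification and not as a demonstrated error. With 5 + 5 health systems and ICC 0.017, the mixed logistic comparison under large-sample inference has type I error of about 7–9% (Wald z about 9%, likelihood ratio 7–8%) against the stated 5%, with intervals about 15% too short relative to t(8). The excess is about 1 point at ICC 0.005, is absent at 0.001, and is larger above 0.017.

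These figures assume equal-sized systems, beta-binomial variation between systems and no adjustment for state. That the sample size contains a few-cluster allowance is inferred from the arithmetic; the article does not say so.

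**What to change.** Add one sentence to Statistical analyses, Patient outcomes: the primary Early versus Delayed comparison uses a logistic model with a random intercept for health system, with tests and confidence intervals from a t reference on between-system degrees of freedom (10 − 2 = 8). A two-sample t-test on the 10 system-level quit rates serves the same purpose. It is the safer choice if the ICC proves much larger than planned, because at ICC 0.10 it held its level in simulation while the model with t(8) did not. Choose one as primary in advance.

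A state-adjusted analysis is optional. With four states it would leave 10 − 2 − 3 = 5 df, and analytic power at 43 per system would be about 72% if adjustment brought no reduction in variance.

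The cost is one sentence and intervals about 2.306 / 1.960 = 1.18 times as wide as normal-based ones. No extra recruitment is needed: power at 43 per system stays at about 80%, as the protocol already states.
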